#### **2. BACKGROUND**

Successful interventions in dyslexia show that reasonable levels of reading accuracy may be attainable (e.g. Tijms et al, 2003; Tijms, 2007; Torgesen, 2005), but no effective cure for the lack of reading fluency is available yet. This may in part be attributed to the fact that the dominant theory of dyslexia assumes a single main cause, a phonological awareness deficit, which never offered a valid explanation for the persistent dysfluency in dyslexia (Blomert & Willems, 2010), but nevertheless inspired and still inspires most reading interventions. A very recent account therefore proposed a core multi-sensory integration deficit in a temporo-parietal network, almost simultaneously affecting superior temporal areas involved in speech processing and fusiform areas involved in visual word recognition (Blomert, in revision). Relevant for present purposes, this new theoretical account also predicts that “ a failure to develop automatic letter-sound integration will first and for all result in an impairment of reading fluency” (Blomert, in revision; Blomert & Froyen, 2010).

Goal of the study is improving reading fluency in dyslexia. We will therefore deliver an intervention focussed on developing of automatic letter-speech sound integration to children with dyslexia, in order to provide a neurocognitive window on the learning mechanisms involved in developing reading fluency.

### **3. STUY OBJECTIVES**

The main objective of study is to determine whether a computer-based intervention focussed on intensively training automation of letter-speech-sound associations can improve reading fluency in children with severe dyslexia.

In more detail, our objectives are:

- Does the intervention improve knowledge of letter-speech sound associations, compared to the no-intervention control group?
- Does the intervention improve automation of letter-speech sound integration, compared to no-intervention control group?
- Does the intervention improve reading accuracy, compared to the no-intervention control group?
- Does the intervention improve reading fluency, compared to the no-intervention control group?
- Are the gains in reading fluency associated with initial levels and/or gains in the automation of letter-speech sound associations?
- Are the intervention-induced reading-related growth curves of the dyslexic children comparable to those of normal readers?
- Does the intervention induce changes in brain responses in a local network related to letter-speech sound processing, as measured by ERPs of audiovisual MMN?
- Does the intervention induce changes in brain responses in a more global neural network for fast visual word processing, as measured by ERPs of visual word recognition?

### **4. RESEARCH METHODS**

#### **4.1. Study Design**

The study is an open randomised controlled trial comparing an intervention addressing letter-speech sound integration to a waiting list control group. Children with severe dyslexia are randomly assigned to either an immediate intervention group or a waiting-list control group by a method of simple randomisation. Participants will be randomised using a computerised random number generator. Children in the intervention condition will receive 34 intervention-sessions in a 19 week period.

In addition, a second control group of normal readers who do not receive the intervention (same age-range, school grade, sociodemographical background, and exclusion criteria as the children with dyslexia) is included in the study.

Behavioural measures of reading, spelling, and letter-speech sound mapping are measured at baseline and at the end of a 19 week (intervention) period for all three groups. EEG measurements of visual word recognition and of letter-speech sound integration are measured at baseline and at the end of the intervention (after 19 weeks) for the intervention group, and only once, at approximately 10 weeks, for both the waiting-list control group and the normal-reader control group (used as a criterion point to compare the pre-post ERP-changes in the intervention with).

## **4.2. Subject Selection**

### **Inclusion Criteria for severe dyslexia**

- Diagnosis of dyslexia (according to criteria of Dutch Dyslexia Foundation, and DSM-IV-TR (reading disorder))
- Suffering from specific and persistent (i.e., failed to respond to remedial support at school) problems with reading at school
- Percentile score  $\leq 10\%$  on a standard reading test
- Age 8-9 years old
- In grade 3 of primary education

### **Inclusion Criteria for normal readers**

- No diagnosis of dyslexia
- Percentile score  $\geq 25\%$  on standard reading test
- Age 8-9 years old
- In grade 3 of primary education
- In the same sample of schools as where the dyslexic children are referred from

### **Exclusion Criteria (for all participants)**

- Behavioral and/or attention disorders, as measured by the Child Behavior Checklist (CBCL)
- $IQ < 85$
- Uncorrected sight problems
- Hearing loss

## **4.3. Number of Participants**

Planned sample size:  $N = 50$  children with severe dyslexia; subjects fulfilling the entry criteria will be randomised to one of the two trial arms.  $N=25$  normal reading children.

## **4.4. Subject Recruitment**

Children with dyslexia will be recruited through the IWAL Institute. Children who (1) are referred by schools to the IWAL Institute because of specific and persistent reading problems at school, (2) received a diagnosis of dyslexia after an extensive cognitive assessment by a psychologist at the IWAL Institute, (3) had a reading score  $\leq 10\%$  on a standard reading test at the diagnostic assessment, and (4) were in grade 3 at school, are recruited.

Normal reading children will be recruited from the same sample of schools as the dyslexic children are referred from.

#### **4.5. Informed Consent**

All participants will receive a consent form. The consent form explains the aims of the study, and the study procedures. The consent form explicitly states that the participant is free to withdraw at any time without any need to give reason.

#### **4.6. Sample size justification**

Before running a sample size analysis, we first calculated the expected effect size for the intervention gains in reading fluency on the basis of the data of previous intervention studies (Tijms, in revision, Saine et al., 2009). These data revealed expected effect sizes in terms of Cohen's  $f$  in the range of 0.33 - 0.40 for gains in reading fluency by intervention in comparison to a no-intervention control group. This is generally considered a medium to large effect size. Therefore, our expected intervention effect size is  $f = 0.33 - 0.40$ .

As we intent to analyse the intervention effects by means of an ANCOVA with pretest scores as covariates for each corresponding posttest score (Vickers & Altman, 2001), we also calculated the  $R^2$  for the covariate pretest score in reading fluency in the study of Tijms (in revision):  $R^2 = .37$ . By including an expected  $R^2$  for the covariate, we were able to calculate the sample size more precisely.

Next, we run a sample size calculation (Power & Precision V4 software; Borenstein, Rothstein, & Cohen, 2001). Our aim is a power of at least 0.80 to detect an intervention effect on reading fluency, assuming the above noted expected effect size ( $f = 0.33 - 0.40$ ), and conducting an ANCOVA with 1 factor (intervention condition, 2 levels) and 1 covariate (pretest level,  $R^2 = .37$ ), and  $\alpha = 0.05$ . The power analysis revealed a power of at least 0.80 for  $n \geq 20$  per intervention condition.

Based on this power calculation and given an anticipated attrition rate of 20%, we aim to recruit a total of 50 dyslexic children.

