#### *Reading*

Word Reading – Accuracy, 3DM (Blomert & Vaessen, 2009)

Word Reading – Fluency, 3DM (Blomert & Vaessen, 2009)

Word Reading Fluency, EMT (Brus & Voeten, 1999)

Text Reading Fluency, SVT-TL (De Vos, 2007)

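### Reading fluency is the main outcome and is powered as one outcome, but it is measured by three unranked tests with no rule for combining them

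*Protocol*

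**What the plan says.** Protocol section 3 sets one main objective: whether the intervention "can improve reading fluency in children with severe dyslexia". It does not say which test measures this.

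Protocol section 4.9, under Reading, lists three fluency measures taken at baseline and posttest: "Word Reading – Fluency, 3DM", "Word Reading Fluency, EMT" and "Text Reading Fluency, SVT-TL". None is ranked above the others.

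Protocol section 4.6 describes the analysis score by score: "we intent to analyse the intervention effects by means of an ANCOVA with pretest scores as covariates for each corresponding posttest score". The same section sizes the trial for one test: "Our aim is a power of at least 0.80 to detect an intervention effect on reading fluency", "conducting an ANCOVA with 1 factor (intervention condition, 2 levels) and 1 covariate", with one effect-size range, one covariate R² (0.37) and alpha 0.05. That is the only place where a significance level appears. The protocol mentions no composite, no multiplicity adjustment and no rule for reading the three fluency results together.

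**The concern.** The sample-size section assumes one fluency outcome, while the measures and the analysis produce three. The three can disagree, for example with a gain on a word list and none on connected text. The protocol then gives no basis for saying whether the main objective was met, and the deciding test could be picked after the data are seen. What is at stake is whether the trial's main answer carries a 5% false-positive rate, and whether the power statement in section 4.6 refers to an identifiable outcome.

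**Working it through.** **Inputs from the protocol (section 4.6).** Cohen's f "in the range of 0.33 - 0.40 for gains in reading fluency by intervention"; covariate R² = 0.37; alpha = 0.05; 20 analysed per arm, so N = 40; power target 0.80; 20% attrition.

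**Inputs assumed.** The correlation r between the three fluency scores after pretest adjustment is not in the documents, so a range is shown. The tests are taken as two-sided, as an ANCOVA F test is.

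**1. The plan's own figure.** Noncentrality λ = N·f²/(1 − R²), with 1 and N − 3 = 37 degrees of freedom.
- f = 0.33: λ = 40 × 0.1089/0.63 = 6.91, power 0.73.
- f = 0.365 (midpoint): λ = 8.46, power 0.81.
- f = 0.40: λ = 10.16, power 0.87.
- Attrition: 40/(1 − 0.20) = 50, as stated.

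So 20 per arm gives 0.80 at the middle and top of the range but not at its lower end. That is a separate matter from the present point. The 0.73 is used below as the power of one fluency test alone at f = 0.33.

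**2. False-positive rate if any one of three at 0.05 counts as success.** With independent tests it is 1 − 0.95³ = 0.143. With correlated tests it comes from simulating three ANCOVA t tests with 37 degrees of freedom:

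| Assumed r | At least one of three significant under no effect |
|---|---|
| 0 | 14.3% |
| 0.5 | about 13% |
| 0.6 | about 12% |
| 0.7 | about 11% |
| 0.8 | about 10% |
| 0.9 | 8.4% to 8.6% between simulation runs |

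Three tests of one skill in the same children are unlikely to be uncorrelated, so 14.3% is an upper bound and not an expected value.

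**3. False-positive rate if all three must be significant.** This cannot exceed 5% (2.3% or less in the simulations for r up to 0.9). Power at f = 0.33 is then only 0.50, 0.56 and 0.59 at r = 0.5, 0.7 and 0.8.

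**4. What one primary outcome would give.** A single named test holds 5% and has power 0.73 at f = 0.33. For the mean of three standardised scores, the effective f is 0.33 × m × 1/√((1 + 2r)/3). Here m is the average effect across the three tests relative to 0.33, and R² = 0.37 is assumed to carry over to the composite. The factor 1/√((1 + 2r)/3) is 1.168, 1.118 and 1.074 at r = 0.6, 0.7 and 0.8.

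| Effect on the three tests | m | Power at r = 0.6 | r = 0.7 | r = 0.8 |
|---|---|---|---|---|
| Equal on all three | 1 | 0.85 | 0.82 | 0.79 |
| Half on one test | 2.5/3 | 0.70 | 0.66 | 0.63 |
| None on one test | 2/3 | 0.51 | 0.48 | 0.45 |

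For example, equal effects at r = 0.6 give f = 0.33 × 1.168 = 0.385, λ = 9.43 and power 0.85. The composite beats a single responsive test (0.73) when effects are similar, and falls below it when one of the three responds little.

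**The case against.** The strongest reply is that the protocol never says each test will be judged at 0.05, or that one significant result is enough. Alpha appears once, as an input to the power calculation, and the per-score sentence only says which covariate goes with which outcome. If all three tests had to be significant, the error rate would stay below 5%. Decision rules and multiplicity procedures are also often left to a statistical analysis plan, which is not shown. All of this stands, and it is why the 8% to 14% is stated conditionally. It does not remove the gap. The outcome on which a trial is powered belongs with the sample-size justification, and that section treats fluency as one outcome while planning an analysis for each score.

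A reader might go further and infer that the plan also loses power. The documents do not support that alongside the inflated error rate, because the two come from different decision rules. Under the unadjusted any-of-three rule, nominal power at f = 0.33 is 0.92, 0.88 and 0.85 at r = 0.5, 0.7 and 0.8. That is above the composite's 0.88, 0.82 and 0.79, and it is bought with the higher error rate.

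A reader might also count all ten behavioural scores and quote a larger error rate. The other seven answer other questions or sit outside the fluency objective, so that figure says nothing about the main answer.

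Finally, preferring a composite to one named test is a judgement. Either would hold 5%.

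**Conclusion.** The point holds in this form: the protocol names no primary fluency test and no combination rule among three tests, although it powers the trial for one. If any one of the three at 0.05 were counted as success, the false-positive rate for the main question would be about 8% to 14% instead of 5%. That range rests on an assumed correlation of 0.9 down to 0 and on a success rule the protocol does not state. That the plan already commits to this rule, or that it loses power, is not shown. The gap should be closed before results are seen.

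**What to change.** In sections 3 and 4.6, name one primary reading-fluency outcome, analysed by ANCOVA with its own baseline as covariate at two-sided 0.05. Report the remaining fluency results as secondary, with confidence intervals. Two choices are open:

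- **One of the three tests.** This is simple and matches the existing power calculation, with power 0.73 at f = 0.33 and 0.87 at f = 0.40 for 20 per arm.
- **The mean of the three scores**, each standardised on the pooled baseline mean and SD of the randomised children, with the baseline composite as covariate. This suits an expectation of similar effects on word and text reading. It loses power if one test responds little, as tabulated above, and the single-test results become supportive only.

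State the reason for the choice and make the effect size and R² in section 4.6 refer to the chosen outcome. No new data are needed. The cost is protocol wording.

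### Power of at least 0.80 with 20 children per arm does not hold over the plan's whole effect range: it is 0.73 at f = 0.33 and reaches 0.80 only from about f = 0.362

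*Protocol*

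**What the plan says.** All inputs stand in Protocol section 4.6.

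- **Effect.** Earlier intervention studies are said to give Cohen's f "in the range of 0.33 - 0.40 for gains in reading fluency by intervention in comparison to a no-intervention control group".
- **Target.** "Our aim is a power of at least 0.80 to detect an intervention effect on reading fluency".
- **Effect used.** The calculation is made "assuming the above noted expected effect size", and the range 0.33 to 0.40 is repeated there in brackets. No single value within it is chosen.
- **Model.** The power is for "conducting an ANCOVA with 1 factor (intervention condition, 2 levels) and 1 covariate", the pretest level with R² = .37, at alpha = 0.05. Sidedness is not stated.
- **Result.** "The power analysis revealed a power of at least 0.80 for" n ≥ 20 per intervention condition.
- **Recruitment.** "Based on this power calculation and given an anticipated attrition rate of 20%, we aim to recruit a total of 50 dyslexic children".

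Section 4.3 repeats the total of 50, and the Appendix B timeline shows 25 children in each dyslexia group.

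**The concern.** A minimum power attached to a range of effects is a statement about the smallest effect in that range. Here that is f = 0.33, and the section does not say that any other value was used. If 20 per arm gives 0.80 only nearer the middle of the range, the printed result does not follow from the printed inputs.

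Section 4.6 is the only justification given for enrolling 50 children. If the true effect lies at the low end of what the plan itself expects, the chance of missing it is about 27%, not at most 20%. A reader of a null result would credit the trial with more sensitivity than it had.

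**Working it through.** **Inputs (section 4.6).** f from 0.33 to 0.40; R² = 0.37; alpha = 0.05, taken as two-sided because the ANCOVA F test is non-directional; n = 20 per arm, so N = 40.

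**Formula.** For one two-level factor and one covariate, the test statistic follows a noncentral F with 1 and N − 3 degrees of freedom and noncentrality λ = f² × N / (1 − R²). Power is the probability that it exceeds the 5% critical value of the central F. For N = 40 the degrees of freedom are 1 and 37, and the critical value is 4.105.

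**Reproducing the plan's figure.** At the midpoint, f = (0.33 + 0.40)/2 = 0.365:

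λ = 0.1332 × 40 / 0.63 = 8.46, power 0.808.

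With 19 per arm the power is 0.787, so 20 is exactly the smallest n that reaches 0.80 at the midpoint. The plan's n = 20 can thus be reproduced, but at f = 0.365 and not at f = 0.33.

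**Across the stated range, 20 per arm.**

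| f | λ = f² × 40 / 0.63 | Power |
|---|---|---|
| 0.33 | 6.91 | 0.726 |
| 0.35 | 7.78 | 0.775 |
| 0.36 | 8.23 | 0.798 |
| 0.362 | 8.32 | 0.802 |
| 0.365 | 8.46 | 0.808 |
| 0.40 | 10.16 | 0.874 |

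Power crosses 0.80 at f of about 0.361. Rounded up so that the bound itself meets 0.80, this is 0.362. The part of the range below it is (0.362 − 0.33)/(0.40 − 0.33) = 0.032/0.07, or roughly 45%.

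**Number needed at f = 0.33.** With 23 per arm power is 0.787. With 24 per arm (N = 48, λ = 0.1089 × 48 / 0.63 = 8.30) it is 0.805. So 24 completers per arm are needed, against 20 planned.

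**Attrition step.** 40 / (1 − 0.20) = 50, which is correct. It means that the plan's own attrition leaves 50 × 0.80 = 40 children, or 20 per arm if allocation and dropout are equal. If nobody were lost (25 per arm), power at f = 0.33 would be 0.821.

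**Other readings at f = 0.33, 20 per arm.**

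| Reading | Power |
|---|---|
| Normal approximation instead of F | 0.748 |
| Noncentrality based on the error degrees of freedom | 0.715 |
| f already adjusted for the pretest, or covariate ignored | 0.53 |
| 0.37 read as a correlation instead of R² | 0.590 |
| One-sided 5% test | 0.825 |

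Only the one-sided test exceeds 0.80. Keeping the two-sided test, R² would have to be about 0.474 instead of 0.37.

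**The case against.** The best defence is that the range was summarised by a central value. The number 20 is exactly what the midpoint requires, and power at the upper end is 0.87. On that view the calculation is sound and the text merely omits the value used. This is probably how the number arose, and it limits the size of the error: the shortfall is at most about 7 percentage points. It does not rescue the sentence, which carries the full range into the calculation and reports a minimum.

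A second defence is that sidedness is not stated and a one-sided 5% test would give 0.825. The section mentions no one-sided test, however, and the F test it names has no direction. A one-sided calculation at f = 0.33 would also have given 19 per arm (0.807), not 20.

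Third, 20 per arm is an expectation. Section 4.1 specifies simple randomisation, which does not guarantee 25 and 25, and dropout may differ between arms. That is right, and the figures here are conditional on equal numbers, as the plan's own are.

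A reader might also go further and infer from the word *gains* that f was standardised on gain scores, so that the pretest is partly counted twice and power is below 0.80 throughout the range. The document does not support this. The word can simply mean improvement due to treatment, the way f was standardised depends on earlier studies not at hand, and any figure would need an assumption about pretest and posttest variances that the plan does not give.

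**Conclusion.** The power statement in section 4.6 is wrong as written. With 20 completers per arm, power is 0.73 at f = 0.33, 0.81 at f = 0.365 and 0.87 at f = 0.40. At least 0.80 is reached only from f of about 0.362, so the claim fails over roughly the lower 45% of the plan's own range.

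This rests on a two-sided F test at 0.05, R² = .37 as stated, f standardised before covariate adjustment (the reading under which the plan's use of R² makes sense), and equal arms with equal dropout.

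It would be too strong to call the sample size indefensible or to say that enrolment must rise. Over the upper part of the range 20 per arm does deliver 0.80, the attrition arithmetic is right, and nothing here biases the estimate or the test. The fault is a planning figure stated for effects at which it does not hold.

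**What to change.** Replace the result sentence in section 4.6 with:

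> With 20 completers per arm (two-sided alpha 0.05, R² = .37), power is 0.73 at f = 0.33, 0.81 at f = 0.365 and 0.87 at f = 0.40; power of at least 0.80 is reached for f >= 0.362.

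Add the value of f on which n = 20 was based. The bound should not be rounded down to 0.36, where power is 0.798.

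The change is to wording only. Enrolment, the attrition allowance and the analysis stay as they are. The cost is that the stated power becomes slightly less favourable at the low end of the range.

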#### **4.7. Intervention**

The intervention in this study is a computerised intervention focussed on the integration of letters and speech sounds in the context of the acquisition of reading fluency. This training is an adaptation of the treatment protocol reported in Tijms (2007). The intervention program is delivered by well-instructed junior psychologists, on a one-to-one basis for 45-minute sessions during a 19 week period. The training frequency is two sessions per week. Intervention takes place at a clinical centre.

## **4.8. Intervention Sites**

This intervention will be conducted at the Rudolf Berlin Center in Amsterdam, and at the associated locations of the IWAL Institute in the Amsterdam area.

## **4.9. Measures**

### **Behavioral measures**

Baseline and posttest:

#### *Reading*

Word Reading – Accuracy, 3DM (Blomert & Vaessen, 2009)

Word Reading – Fluency, 3DM (Blomert & Vaessen, 2009)

Word Reading Fluency, EMT (Brus & Voeten, 1999)

Text Reading Fluency, SVT-TL (De Vos, 2007)

#### *Spelling*

Spelling – Accuracy, 3DM (Blomert & Vaessen, 2009)

Spelling – Fluency, 3DM (Blomert & Vaessen, 2009)

#### *Letter-Speech Sound Mapping*

Letter-Speech Sound Identification – Accuracy, 3DM (Blomert & Vaessen, 2009)

Letter-Speech Sound Identification – Fluency, 3DM (Blomert & Vaessen, 2009)

Letter-Speech Sound Discrimination – Accuracy, 3DM (Blomert & Vaessen, 2009)

Letter-Speech Sound Discrimination – Fluency, 3DM (Blomert & Vaessen, 2009)

Baseline only:

Child Behavior Checklist (CBCL, Achenbach & McConaughy, 2003)

Coloured Progressive Matrices (Raven, Raven, & Court, 1998)

Behavioural measures are tested individually at either the clinical centre for the dyslexic children or at school for the normal readers during one session of approximately one hour. Children are tested in a silent room. The Child Behavior Checklist is completed by parents via a web-based form.

